Despite the acceptability of VR in children and the sustained effects of rTMS, it is currently unknown whether there is a synergistic effect of the combination of VR therapy and rTMS on pain in children with spastic CP. This study protocol combined VR therapy and rTMS with the aim of exploring the efficacy and safety of this combined treatment in improving the pain and motor development of children with spastic CP. We hypothesize that rTMS can improve pain in children with CP and that the combination of VR therapy and rTMS will show better efficacy than rTMS alone.

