### Sample size

G*Power 3.1 software was used to calculate the sample size. Based on Sahin [37] et al., the effect size was set to 0.9, with α = 0.025 and β = 0.1. Two sets of comparisons will be conducted (the VR + rTMS group vs. the rTMS group and the rTMS group vs. the control group). Considering a potential dropout rate of 15%, a total of 147 children (49 in each group) will be enrolled in this study.

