### Statistical analysis

#### Main analysis

The R-FLACC scores before and after the intervention will be compared to determine the therapeutic effects in the three groups. Subjects in randomly assigned groups with baseline measurements will be enrolled in the analysis of primary outcomes using the following method.

 [1] All indicators will be analysed as continuous variables.

 [2] Boxplots will be used to detect outliers, the S‒W test will be used to test distribution normality, and Levene’s test will be used to test the homogeneity of variance.

 [3] A paired-sample t test will be used to analyse the difference in outcomes with data conforming to a normal distribution and homogeneous variance before and after the intervention. The Wilcoxon signed-rank test will be used to examine the difference before and after intervention for outcome measures that do not conform to a normal distribution or exhibit heterogenous variance.

 [4] The difference between the outcome measures of each group before and after the intervention will be calculated. An independent-sample t test will be used to analyse the difference between the groups if the differences are normally distributed and exhibit homogeneous variance; otherwise, the Wilcoxon signed-rank test will be used.

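### Testing the two planned primary contrasts by Holm's procedure, instead of at a flat 0.025 each, would raise power at the same family-wise error and with no extra patients

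*Protocol article*

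**What the plan says.** The Introduction of the protocol article closes with a two-part hypothesis: "We hypothesize that rTMS can improve pain in children with CP and that the combination of VR therapy and rTMS will show better efficacy". In the second part the comparator is rTMS given without VR. The Sample size section matches it: "the effect size was set to 0.9, with α = 0.025 and β = 0.1. Two sets of comparisons will be conducted", namely VR + rTMS against rTMS and rTMS against control. The Ethics section names the same two contrasts. Neither section says whether 0.025 is one- or two-sided, why it was chosen, or whether one contrast ranks above the other.

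Under Statistical analysis, the Main analysis says that R-FLACC scores before and after the intervention "will be compared to determine the therapeutic effects in the three groups". Item [4] then states: "An independent-sample t test will be used to analyse the difference between the groups", applied to the change in each outcome. It gives no significance level, names no contrasts, and does not say what result would support the hypothesis.

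**The concern.** The one level that the protocol fixes, 0.025 for each of two contrasts, is a valid way to share 0.05 but not the most powerful one. Holm's step-down procedure gives the same guarantee and can only add rejections. The difference counts here because the hypothesis has two parts. Full support needs both contrasts to succeed, and joint success is where a flat split loses most.

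Item [4] is also the place where the primary test is defined, and it does not carry over the level or the contrasts from the Sample size section. The decision rule is therefore best written there, so that a contrast with p between 0.025 and 0.05 has an agreed reading before the data are seen.

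**Working it through.** **Inputs from the protocol article.** Effect size 0.9, α = 0.025 per contrast, β = 0.1, two contrasts, 15% dropout (Sample size); equal allocation to three arms (Study design). Enrolment is given as 49 per group (Sample size) and as 36 per group (Ethics). That conflict is a separate matter, so both are carried through.

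**Step 1: what does α = 0.025 mean?** The normal-approximation size per arm is n = 2(z₁₋α/₂ + z₁₋β)² / d².
- Two-sided 0.025: 2 × (2.241 + 1.282)² / 0.81 = 30.6, so 31 per arm. The exact t calculation gives 32.
- 31 × 1.15 = 35.65, so 36 per group, which is the Ethics figure.
- 147 is reached only by adding two separate two-arm trials: 2 × (32 + 32) = 128, and 128 × 1.15 = 147.2. This counts the shared rTMS arm twice.
- One-sided 0.025 gives 26 to 27 per arm, or 30 to 32 with dropout, and matches neither total.

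Both stated totals thus trace back to two-sided 0.025 per contrast, an even split of 0.05.

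**Step 2: evaluable numbers.** 36 × 0.85 = 30.6, taken as 30. 49 × 0.85 = 41.65, taken as 41.

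**Step 3: family-wise error.** Three arms were simulated 400,000 times with normal data and pooled-variance t tests. The shared rTMS arm gives the two contrasts a correlation of −0.5.

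| Rule, no true effects | Family-wise error |
|---|---|
| Two named contrasts, flat 0.025 | 4.6% |
| Two named contrasts, Holm | 4.6% |
| Three pairwise tests at 0.025 | 6.4% |
| Two contrasts at 0.05 | about 9% |
| Three pairwise tests at 0.05 | about 12% |

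With one contrast null and the other at 0.9 (41 per arm), Holm rejects the null contrast in 4.8% of trials, still under 5%.

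**Step 4: power at the planned effect.** Both contrasts have a true effect of 0.9 (standardised means 1.8, 0.9 and 0).

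| Evaluable per arm | Outcome | Flat 0.025 | Holm |
|---|---|---|---|
| 30 | each contrast | 0.88 | 0.93 |
| 30 | both contrasts | 0.76 | 0.86 |
| 41 | each contrast | 0.96 | 0.98 |
| 41 | both contrasts | 0.92 | 0.96 |

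The results are internally consistent. Holm adds a rejection only when one p is at or below 0.025 and the other lies between 0.025 and 0.05. The gain in joint success must therefore equal the sum of the two per-contrast gains. At 30 per arm, 0.8575 − 0.7599 = 0.0976, and the per-contrast gains are 0.0488 + 0.0488 = 0.0976.

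Power to win at least one contrast is identical under both rules (0.998 at 30 per arm), because Holm's first step is the flat test.

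**Step 5: a smaller effect (assumption).** If both true effects were 0.5, joint success would rise from 0.07 to 0.14 at 30 per arm and from 0.17 to 0.29 at 41. Per-contrast power would rise from 0.36 to 0.40 and from 0.49 to 0.55.

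**The case against.** The strongest reply is that nothing is broken. The Sample size section gives the level, and both it and the Ethics section name the two contrasts as comparisons that will be carried out. Item [4] is silent; it does not contradict them. A condensed article may leave the level and the multiplicity method to an analysis plan that is not shown. A flat 0.025 is valid, easy to explain, and comes with matching 97.5% intervals. All of this stands, and it is why the point is about efficiency only.

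Three stronger readings are tempting, and the documents support none of them.
- A reader might infer that item [4] means all three pairwise tests. It states no number of tests, and the Sample size section supplies the number: two.
- A reader might infer that the primary analysis inflates the family-wise error. The 9% and 12% figures need a level of 0.05, and the 12% needs a third contrast as well. The protocol states neither. A third contrast alone, at 0.025, gives 6.4%.
- A reader might infer that the flat split pushes joint power below the 90% planned for each contrast. That holds at 36 enrolled per group (0.76) but not at 49 (0.92).

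It is also fair to say that no passage calls the two contrasts equal in rank. That is inferred from the two-part hypothesis and the absence of any order. A fixed testing order would also be legitimate if the investigators wanted one, but the document gives none.

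**Conclusion.** Holm on the two named contrasts is a better choice than the flat split, by a modest margin. At the planned effect it adds about 5 points per contrast and 10 points for joint success with 30 evaluable per arm, and about 2 and 4 points with 41. It adds nothing to the chance of at least one success. Family-wise error stays at or below 5% under either rule, so this is not an error-rate repair.

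The conclusion assumes that 0.025 is two-sided, that the two contrasts rank equally, and that the effect size of 0.9 applies to the change score tested in item [4]. The power figures further assume normal data and equal variances. The ordering of the two procedures does not: Holm rejects whatever the flat split rejects, whichever valid two-sample test supplies the p-values.

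Rating: cheap improvement.

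**What to change.** Add to item [4], before any outcome data are compared by group, wording to this effect:

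> The primary analysis consists of two two-sided contrasts on the change in R-FLACC total score: VR + rTMS versus rTMS, and rTMS versus control. They are tested by Holm's procedure at a family-wise level of 0.05: the smaller p-value against 0.025 and, if that is significant, the other against 0.05. The study hypothesis is supported in full only if both are significant; otherwise the claim is limited to the significant contrast.

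Keep α = 0.025 in the Sample size section as the conservative sizing level, and say there that it is two-sided.

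The cost is one or two sentences, with no new data and no added patients. The one drawback is in reporting, since intervals that match Holm exactly are less simple. Report 97.5% intervals alongside, and note that a contrast won at the second step with p between 0.025 and 0.05 will have a 97.5% interval that includes zero, so the Holm test decides.

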## Methods

### Study design

This is a randomized, single-blind (evaluator), prospective clinical trial (protocol version 2.0, date: 2023.02.28). Participants will be randomly and equally divided into 3 groups: the VR + rTMS group, the rTMS group, and the control group. Two 4-week sessions of treatment will be provided to participants, separated by an interval of one week. Assessments will be performed at baseline (week 0) and after the intervention (week 9). This study will follow the Standard Protocol Items: Recommendations for Intervention Trials (SPIRIT) guidelines [32] (Fig. 1) and the Consolidated Standards of Reporting Trials (CONSORT) statement (http://www.consort-statement.org (Fig. 2) [33]. The study’s trial registration number is ChiCTR230069853.

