#### Secondary analysis

Data will be divided into an intention-to-treat analysis set and a safety analysis set. The intention-to-treat set will include subjects who were randomly assigned to groups and completed the baseline measurement. Subjects who received at least one intervention and underwent one safety assessment will be allocated to the safety analysis set. The change in secondary outcomes from before to after the intervention will be compared to determine the therapeutic effects in three groups using the intention-to-treat set through the same analytical method as the main analysis. The safety analysis will include counting the number of adverse events and the number of patients who drop out because of unbearable adverse events.

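### The fallback for comparing two independent arms is the Wilcoxon signed-rank test, a paired test, and on the primary pain scale it may well be invoked

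*Protocol article*

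**What the plan says.** All of this is in the Statistical analysis part of the protocol article.

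- **Main analysis, item [2]:** the Shapiro-Wilk test "will be used to test distribution normality", and Levene's test checks equality of variance.
- **Item [3], within a group:** a paired t test if both conditions hold. If not, "The Wilcoxon signed-rank test will be used to examine the difference before and after intervention".
- **Item [4], between groups:** each child's before-after difference is calculated, and arms are compared by a t test for independent samples when those differences pass both checks. The closing clause covers every other case: "exhibit homogeneous variance; otherwise, the Wilcoxon signed-rank test will be used".
- **Secondary analysis:** changes in the secondary outcomes are compared "using the intention-to-treat set through the same analytical method as the main analysis".

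On the design, the Study design section says "Participants will be randomly and equally divided into 3 groups", and the Sample size section says "Two sets of comparisons will be conducted (the VR + rTMS group vs. the rTMS group and the rTMS group vs. the control group"). The primary outcome is the R-FLACC total: five dimensions scored 0 to 2, so an integer from 0 to 10.

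**The concern.** Items [3] and [4] name the same non-parametric test for two different problems. In item [3] each child supplies a before and an after value, so a paired test is right. In item [4] the two samples are different children in different arms, and nothing links a given child in one arm to a given child in the other.

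The conditions that lead to the fallback are also poorly chosen. Unequal variance alone sends item [4] to a rank test, although Welch's t test deals with it directly. Item [3] requires equal before and after variances, which a paired t test does not assume.

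At stake is the p-value for both planned comparisons on the primary outcome. If a gate test rejects, the analyst must either follow a rule that does not work or depart from the published plan after seeing the data. Because the gates are applied to the trial data, it is not known beforehand which test will carry the primary conclusion.

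**Working it through.** The plan states no figure to reproduce here; the error is in the test named. The calculations below show its consequences.

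**Inputs**
- Significance level 0.025, effect size 0.9, dropout 15% (Sample size section). Sidedness is not stated; two-sided is assumed.
- Group size: 49 per group (Sample size section) or 36 per group (Ethics section). These contradict each other and need separate reconciliation, so both are used. Evaluable: 49 × 0.85 = 41.65, about 41; 36 × 0.85 = 30.6, about 30.
- Assumed, because the article does not give them: gate level 0.05; latent R-FLACC mean 2 to 5 and SD 1.0 to 3.0; pre-post correlation 0.5.

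**1. What the test would do in item [4]**
- *Across arms, unequal sizes.* Pairs cannot be formed; 41 against 39 values gives an error. If completers are analysed and each child drops out independently with probability 0.15, the probability that two arms of n children end up unequal is 1 − Σₖ [C(n,k) 0.85^k 0.15^(n−k)]². This is 0.868 for n = 36 and 0.887 for n = 49.
- *Across arms, equal sizes.* The test runs, but on whatever pairing the record order produces.
- *Within each arm.* It tests change from baseline, which is not a comparison between arms.

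**2. How far the p-value moves with record order**

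One simulated data set, 41 per arm, changes drawn from Normal(−1, SD 2) and Normal(−2.1, SD 2) and rounded to integers. The standardised effect is 1.1/2 = 0.55.

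| Test | p-value |
|---|---|
| Rank-sum | 0.013 |
| Signed-rank, 5,000 random pairings: minimum | 0.0005 |
| 2.5th percentile | 0.003 |
| Median | 0.012 |
| 97.5th percentile | 0.029 |
| Maximum | 0.057 |

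About 94% of pairings fall below 0.025 and 6% do not, with the data unchanged.

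Over repeated data sets with one arbitrary pairing each, signed-rank and rank-sum disagree at 0.025 in about 9% of trials at effect 0.55. At the planned 0.9 they disagree in about 3% (41 per arm) or 5% (30 per arm), and under no effect in about 1%. Average type I error of the signed-rank test is 0.023 to 0.025.

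**3. How often the fallback would be reached**

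Scores were simulated as integers limited to 0 to 10. The fallback counts as triggered for one pairwise comparison if Shapiro-Wilk rejects in either arm or Levene's test rejects.

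| Evaluable per arm | Range over 20 scenarios | Scenarios above 50% |
|---|---|---|
| 30 | 25% to 99.8% | 12 |
| 41 | 28% to 100% | 16 |

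That is 28 of 40 scenarios. A repeat with the gates applied to integer change scores gave 23% to 100%, above half in 26 of 40. The frequency is highest when the SD is small (about 68% to 100% at SD 1.0 to 1.5) or mean pain is low. It falls to about 25% to 40% at mean 4 to 5 with SD 2.5 to 3. Coarse integer data failing Shapiro-Wilk is the main cause: where the two gates were separated (SD 1.0 to 2.0), Levene's test rejected in only 2% to 5%. Low scores are possible because entry needs only a history of pain, with no minimum R-FLACC score.

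**4. What the correct test would do**

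At effect 0.9, two-sided 0.025 and 41 per arm, the rank-sum test has simulated type I error 0.024 and power 0.953. Its efficiency for normal data is 0.955, so where the t test needs 32 evaluable per arm for 90% power, the rank-sum test needs 32/0.955 = 33.5, or 34. Enrolled at 15% dropout, that is 34/0.85 = 40 per arm.

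**The case against.** The strongest reply is that this is a slip of one word. The same sentence names an independent-sample t test, so rank-sum was presumably meant, and software would refuse to run the test on unequal arms rather than return a wrong answer. With a pairing unrelated to the outcomes, average type I error is near nominal and power is almost that of the rank-sum test (0.940 against 0.945 at effect 0.9, 41 per arm). The illustration uses effect 0.55, which puts p close to the threshold. The article gives no mean or SD for R-FLACC, so the frequency of the fallback rests on assumptions. Unequal sizes presuppose a completer analysis, whereas the article includes every randomised child with a baseline measurement, and handling of missing values may be set out elsewhere. Finally, the gates and branches are written down in advance, and a preference for Welch's test or a baseline-adjusted model is only a preference.

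Most of these limits stand. The fault is not inflated average error, the illustration is a borderline case, and the points on Welch's test, the gates and item [3] are improvements rather than corrections. Use of the signed-rank test in item [3] is itself legitimate. The central point is unaffected: a specific test is named for the primary between-group comparison, it does not fit the design, and nothing else in the article corrects it. A wrong rule stated outright is not detail left to an analysis plan. That it is probably a slip makes it easy to repair, but the repair should be made before the data are seen.

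**Conclusion.** The concern holds. As written, the between-group fallback for the primary outcome, and through the Secondary analysis for every secondary outcome, is a paired test on unpaired groups. Its result is undefined when the analysed numbers differ and depends on record order when they do not. Used within arms, it answers a different question.

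The test name is wrong whatever is assumed. How often that matters depends on the unknown distribution of R-FLACC: on the assumed values the fallback is triggered in roughly a quarter to all trials, and more often than not in 26 to 28 of 40 scenarios. The 87% to 89% chance of unequal arms assumes independent 15% dropout and analysis of completers.

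**What to change.** **Minimum change.** In item [4], replace the signed-rank test with the Wilcoxon rank-sum (Mann-Whitney) test. Item [3] can keep the signed-rank test. The Secondary analysis inherits the correction because it refers back to the same method.

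**Better.** Drop the Shapiro-Wilk and Levene gates and fix one primary between-group analysis in advance that tolerates unequal variance: Welch's t test on the change scores, or a linear model adjusted for baseline with robust standard errors. Keep the rank-sum test as the sensitivity analysis and apply the same rule to the secondary outcomes. If the gates are kept, unequal variance alone should lead to Welch's test, and the equal-variance condition for the paired t test in item [3] should go.

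**Cost.** One or two sentences of analysis wording. No further children are needed on this account if 49 per group are enrolled: the rank-sum test then has about 95% power at effect 0.9 with 41 evaluable. With 36 per group (30 evaluable) its power is about 86%, against about 88% for the t test. That shortfall from 90% comes mainly from the smaller total and belongs with the reconciliation of 108 and 147.

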#### Secondary analysis

Data will be divided into an intention-to-treat analysis set and a safety analysis set. The intention-to-treat set will include subjects who were randomly assigned to groups and completed the baseline measurement. Subjects who received at least one intervention and underwent one safety assessment will be allocated to the safety analysis set. The change in secondary outcomes from before to after the intervention will be compared to determine the therapeutic effects in three groups using the intention-to-treat set through the same analytical method as the main analysis. The safety analysis will include counting the number of adverse events and the number of patients who drop out because of unbearable adverse events.

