#### Safety

Before the start of treatment, we will record the children’s history of seizures, syncope, headache, cognitive deficits, and behavioural disorders in detail. For children with adequate cognitive ability, subjective evaluation of treatment tolerance will be used to evaluate safety during and after treatment on a scale of 1 to 10, where 1 is the least pleasant and 10 is the most pleasant. If the score is less than 5 points, this reflects poor treatment tolerance, and the treatment will be stopped. For children with cognitive deficits, physiotherapists will observe the child’s expression during each treatment. According to the FPS-R, treatment should stop when there is frowning or deepening of the nasolabial groove on children’s faces. If mild adverse events occur (fatigue, local discomfort, headache), the treatment will be paused, the event will be recorded, and the treatment intensity will be adjusted. If severe adverse events (e.g., seizure) occur, the treatment will be stopped, emergency treatment will be provided, and the condition will be reported to the research leader.

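### The intention-to-treat set needs only a baseline score, but every listed test needs a week 9 score, so children without one enter no stated test

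*Protocol article*

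**What the plan says.** **Population.** Protocol article, Main analysis: "Subjects in randomly assigned groups with baseline measurements will be enrolled in the analysis of primary outcomes using the following method". Secondary analysis gives the same criterion its label: "The intention-to-treat set will include subjects who were randomly assigned to groups and completed the baseline measurement". It then applies the main method to the secondary outcomes in that set.

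**Method.** Within groups (Main analysis, item 3): "A paired-sample t test will be used to analyse the difference in outcomes", with a signed-rank fallback. Between groups (item 4): "The difference between the outcome measures of each group before and after the intervention will be calculated", and then "An independent-sample t test will be used to analyse the difference between the groups if the differences are normally distributed", with a Wilcoxon fallback.

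**Timing.** Study design schedules outcome assessment at week 0 and week 9 only.

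**Attrition.** Sample size: "Considering a potential dropout rate of 15" per cent, leading to 147 children (49 per group). Ethics uses the same 15% but gives 108 (36 per group). Safety has rules for ending treatment; for a low tolerance score, "this reflects poor treatment tolerance, and the treatment will be stopped". Secondary analysis also plans to count children who leave because of intolerable adverse events. The article does not say whether a child whose treatment was stopped is still assessed at week 9.

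**The concern.** The population and the tests are tied together in one sentence of Main analysis, and they do not fit. A child with a baseline score and no week 9 score belongs to the set but has no pair and no difference. There is no intermediate visit to draw on. Run as written, the tests use completers while the result carries an intention-to-treat label.

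Who is lost matters more than how many. The article itself foresees children leaving because of adverse events. For children with cognitive deficits, treatment is stopped on facial signs of discomfort, and facial expression is one of the five R-FLACC dimensions. Loss could therefore be related to both treatment and outcome. If it differs between arms, a comparison of completers no longer has the protection of randomisation.

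**Working it through.** **1. Can each stated test use a child without a week 9 score?**

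| Stated analysis (Main analysis) | Needs | Child with baseline only |
|---|---|---|
| Paired t or signed-rank, within group | week 0 and week 9 | not used |
| Independent t or Wilcoxon on differences, between groups | week 9 minus week 0 | not used |
| Secondary outcomes, same method | both | not used |

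**2. The plan's own sample size.** Inputs from Sample size: d = 0.9, α = 0.025 (taken as two-sided; the article does not say), power 90%.

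- n per group = 2(2.241 + 1.282)² / 0.9² = 30.6, so 31; the t-based version gives 32.
- With 15% dropout: 31/0.85 and 32/0.85 give 37 and 38; 31 × 1.15 and 32 × 1.15 give 36 and 37.

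The 36 in Ethics is reproduced; the 49 in Sample size is not. That conflict is a separate matter, so both sizes are carried below.

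**3. How many could be left out at 15%?**

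- 108 × 0.15 = 16.2 children; 36 × 0.85 = 30.6 left per group.
- 147 × 0.15 = 22.05 children; 49 × 0.85 = 41.65 left per group.

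**4. Power.** At d = 0.9 and two-sided 0.025, power is 93.4% with 36 and 87.9% with 30 per group, or 98.4% with 49 and 96.2% with 41. The inflation covers most of the loss, so power is not the main issue.

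**5. Bias.** Let a fraction p of an arm be missing, and let those children have improved k SD less than completers. The mean over all randomised is m − pk when the completer mean is m, so completers overstate that arm by pk. For a contrast, bias = p₁k₁ − p₀k₀. The values of k are assumptions; the documents give none.

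- rTMS versus control, p = 0.15 in both arms, sham loss random (k₀ = 0): 0.15 × 0.5 = 0.075 SD; 0.15 × 1.0 = 0.15 SD. Against the planned 0.9 SD this is 8% to 17%.
- VR + rTMS versus rTMS, same p and k in both arms: 0.
- VR + rTMS versus rTMS if VR adds selective loss, for example 20% against 10% at k = 1: 0.20 − 0.10 = 0.10 SD.
- Reverse case, poor responders leave sham only, k = 1: −0.15 SD, against treatment.

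**6. Simulation under assumed dropout.** No true effect, 15% missing per arm, two-sided 0.025, baseline to week 9 correlation 0.5. Active-arm dropout is weighted by exp(−g × improvement); sham loss is random. For rTMS versus control:

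| Setting | Bias (SD) | Rejection rate |
|---|---|---|
| Random loss in both arms | about 0 | 2.2% to 2.7% |
| Change-score t test, g = 1 | about 0.14 | 5% to 6% |
| Change-score t test, g = 2 | about 0.20 | 9% to 12% |
| Baseline-adjusted ANCOVA with imputation, g = 1 to 2 | 0.10 to 0.16 | 5% to 9% |
| Week 9 obtained in everyone | about 0 | about 2.5% to 3% |

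The g = 2 row is a stress case: 0.20/0.15 implies a gap of about 1.3 SD, beyond the 0.5 to 1.0 range in step 5. With equal weighting in both active arms, the mean bias in VR + rTMS versus rTMS was about zero.

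**7. What the sensitivity analysis could cost.** If the 15% missing from the active arm had control-level change, the effect over all randomised would be 0.9 × 0.85 = 0.765 SD. Power with the SD unchanged is then 93.3% at 49 and 82.8% at 36 per group.

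**The case against.** The strongest reply is that a set says who is analysed and a test says how. An imputation rule would supply the missing week 9 values, after which the same tests run on the full set. Such rules commonly sit in a full protocol or analysis plan, neither of which is shown. This stands to the extent that a missing imputation rule alone is no finding. What remains is that the article states both a population and a method, and the method cannot use everyone in the population without a further step.

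Three stronger readings are tempting, and the documents do not support them.

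- A reader might infer that the primary analysis is completers-only by design. The article says the opposite about enrolment into the analysis and nowhere excludes children without week 9 data.
- A reader might infer that 15% of week 9 scores are expected to be missing. The figure is a potential dropout rate used to size the trial. Safety stops treatment, not follow-up, so stopped children may still be assessed.
- A reader might infer that both primary contrasts are biased towards treatment. Only one has a sham arm, and equal selective loss in the two active arms cancels. The direction is also uncertain: the tolerance rules apply to all arms, the sham is described as matching in sound and vibration, the Discussion describes a similar rTMS programme as well tolerated, and sham families may leave for lack of benefit.

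It is also fair to say that ANCOVA with imputation from baseline alone does not cure outcome-related dropout. Step 6 confirms this, and it determines what the fix must lead with.

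**Conclusion.** The point holds as a misfit between stated set and stated tests, for the primary outcome in Main analysis and, by extension, for the secondary outcomes. Unless a rule exists elsewhere, up to about 15% of randomised children (16 of 108 or 22 of 147) could be absent from a result labelled intention-to-treat. That upper figure assumes that every dropout lacks a week 9 score.

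The consequence is possible bias and a mislabelled population. For rTMS versus control the overstatement is about 0.075 to 0.15 SD if active-arm dropouts would have improved 0.5 to 1.0 SD less and sham loss is random. For VR + rTMS versus rTMS there is no mean bias unless VR adds selective dropout. These gaps are assumptions, and the sign could reverse. The plan should be changed: the remedy is cheap, and week 9 data not collected cannot be recovered afterwards.

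**What to change.** 1. State that week 9 R-FLACC is sought in every randomised child, including those whose treatment was stopped. This comes first because it is the only step that removes the problem at source.
2. Replace the change-score tests as the primary analysis with baseline-adjusted ANCOVA in all randomised children, using multiple imputation for missing week 9 values. This makes the analysis match the set.
3. Add a sensitivity analysis in which active-arm children without week 9 data receive control-arm values, because imputation from baseline alone leaves outcome-related dropout bias in place.
4. Keep the before-after difference tests if wanted, labelled as a completer analysis.

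**Cost.** Changes to the protocol and analysis-plan wording, some effort to retrieve week 9 scores, and some extra analysis. No new visit is needed, since week 9 is already scheduled.
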